### Primary outcome

#### Pelvic pain

The primary outcome is pelvic pain that include dysmenorrhea, intermenstrual pain and dyspareunia. They will be assessed on a VAS scale [14]. On the VAS scale, a 100-mm horizontal line from no pain on the far left to the worst possible pain on the far right is scored by determining the distance from the far left to the edge of the mark made by the patient. The distance represents pain intensity. The VAS will be assessed at baseline, the first, second and third menstrual cycles and the follow-up period. See Table 2 for the study design schedule.

**Table 2 Tab2:** Study design schedule

Period	Inclusion	Treatment			Follow-up		
Visit	1	2	3	4	5	6	7
Menstrual cycle	0 month	1	2	3	4	5	6
Patients	√						
Inclusion and exclusion criteria	√						
Informed consent	√						
Physical examination	√			√			
Medical history	√						
Comorbidities	√	√	√	√	√	√	√
VAS	√	√	√	√	√	√	√
EHP-30	√			√			√
MPI	√			√			√
BDI and POMS	√			√			√
PGIC	√			√			√
Pain diary	√	√	√	√	√	√	√
Patient compliance				√			√
Reasons for dropout or withdrawal				√			√
Adverse events				√			
Safety evaluation							√

*BDI* Beck Depression Inventory, *EHP* Endometriosis-specific quality of life, *MPI* Multidimensional Pain Inventory, *PGIC* Patient Global Impression of Change, *POMS* Profile of Mood States, *VAS* Visual Analog Scale

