### Sample size calculations and statistical analysis

This trial will use a clinical-superiority design that aims to verify that the curative effect of acupuncture is better than that of comfort needles. The primary outcome measure is proposed to be the VAS. The minimal important difference (MID) for improvement on the VAS was found to be − 3.9 cm and/or − 49% [20]. According to our pre-experimental treatment of women with pain related to endometriosis, assuming the standard deviation (SD) to be 1.7 and the difference between two treatment effect to be 3, the statistical power is 80% and the significance level is 0.05. According to the formula [21]:$$ N=2\times {\left[\left({Z}_{1-\alpha }+{Z}_{1-\beta}\right)/\left(\delta -{\delta}_0\right)\right]}^2\times {S}^2, $$

where *N* represents size per group, *Z*_1-α_ is Type I error, *Z*_1-β_ is Type II error, *δ* is expected SD of the population being sampled, *δ*_0_ is tolerable error in distance from mean value and *S*^2^ is SD. So it requires each group to contain no less than 44 patients. With an estimated 20% dropout rate, we plan to recruit 53 patients for each group, for a total of 106 patients.

Data will be summarized with counts for categorical variables present as mean and SD for normally distributed variables, or median (interquartile) for the variables not normally distributed. Missing data will be imputed according to the last-observation-carried-forward (LOCF) [22] principle. The data will be subjected to intent-to-treat analysis. A statistician blinded to the group settings will perform the statistical analysis. The between-group difference will be compared by analysis of covariance. The variables not normally distributed will be assessed by the rank-sum test. If participants have taken analgesics during the trial, they will be excluded from the analysis and the rate difference of outcomes between the two groups will be analyzed. Statistical significance will be set at *P* < 0.05.

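### The observed distribution of the primary VAS decides whether it is tested by ANCOVA or by an unadjusted rank-sum test; ANCOVA on baseline VAS should be fixed in advance

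*Protocol article*

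**What the plan says.** All of the analysis rules are in the protocol article, under Sample size calculations and statistical analysis.

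- Endpoint: "The primary outcome measure is proposed to be the VAS".
- Main test: "The between-group difference will be compared by analysis of covariance". No covariate is named.
- Fallback: "The variables not normally distributed will be assessed by the rank-sum test". No outcome is excluded from this rule, and no normality test or cut-off is given.
- Sizing: "assuming the standard deviation (SD) to be 1.7 and the difference between two treatment effect to be 3", and "the statistical power is 80% and the significance level is 0.05".

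Under Pelvic pain the article adds: "The VAS will be assessed at baseline, the first, second and third menstrual cycles and the follow-up period". A baseline value is therefore collected for every patient and is the natural covariate, although that is an inference.

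**The concern.** A confirmatory trial should know its primary test and its primary effect measure before the data are seen. Here both depend on how the VAS scores turn out.

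1. **The trigger is misplaced.** ANCOVA assumes roughly normal residuals, not a normally distributed outcome. Two normal groups with different means form a mixture, which can look non-normal because the treatment works. Relief also pushes scores towards zero, where the scale is bounded.
2. **The question changes.** ANCOVA estimates an adjusted mean difference in cm. A standard rank-sum test compares the two distributions by ranks and gives no such estimate. The result could not be set directly against the planned difference or the minimal important difference, both of which are in cm.
3. **Baseline information is dropped.** A standard rank-sum test on outcome scores takes no covariate, so whatever precision baseline VAS would have bought is lost.

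**Working it through.** **Reproducing the plan's 44.** The article's formula is N = 2 × [(Z(1−α) + Z(1−β))/(δ − δ0)]² × S². With one-sided α = 0.05 (Z = 1.645), 80% power (Z = 0.842), S = 1.7, δ = 3 and δ0 = 3.9:

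N = 2 × (2.4865/0.9)² × 2.89 = 44.1, which matches 44.

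Taking δ0 = 3.9, the stated minimal important difference, is an inference. With δ0 = 0 the same formula gives about 4 per group. The difference that drives N = 44 is therefore |3 − 3.9| = 0.9 cm, and the power comparison uses it.

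**Power under normality** (44 per group, two-sided 0.05, difference 0.9 cm, noncentral t). The baseline-to-outcome correlation r is not in the article. It is assumed to be 0.3 to 0.7, with SD 1.7 read as that of outcome scores.

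- ANCOVA: residual SD = 1.7 × √(1 − r²); standard error = residual SD × √(2/44).
- Rank-sum: relative efficiency 0.955, so effective SD = 1.7/√0.955 = 1.740; standard error 0.371; ratio 0.9/0.371 = 2.43; power about 67%.

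| r | ANCOVA residual SD | Standard error | 0.9/SE | ANCOVA power | Rank-sum power |
|---|---|---|---|---|---|
| 0.3 | 1.622 | 0.346 | 2.60 | 73% | 67% |
| 0.5 | 1.472 | 0.314 | 2.87 | 81% | 67% |
| 0.7 | 1.214 | 0.259 | 3.48 | 93% | 67% |

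At a true difference of 3 cm both tests have about 100% power.

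**Power when the fallback is likely to fire.** The rule applies to non-normal data, so the normal case alone is not enough. The table below gives simulation results (3,000 trials per row, 44 per group, difference 0.9 cm) in %. The switch goes to rank-sum when a Shapiro-Wilk test on the outcome has p < 0.05; this test is an assumption, since the article names none.

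| Data | r | ANCOVA | Rank-sum | Switch rule | Switch fires |
|---|---|---|---|---|---|
| Normal | 0.3 | 73.0 | 66.9 | 72.6 | 5.2 |
| Normal | 0.5 | 80.1 | 67.4 | 79.4 | 5.3 |
| Normal | 0.7 | 93.5 | 66.6 | 91.6 | 5.4 |
| Skewed (gamma) | 0 | 67.8 | 82.4 | 82.4 | 98.2 |
| Skewed (gamma) | 0.3 | 73.2 | 79.7 | 79.8 | 95.1 |
| Skewed (gamma) | 0.5 | 79.8 | 75.5 | 76.5 | 87.2 |
| Skewed (gamma) | 0.7 | 92.1 | 75.3 | 78.3 | 83.7 |
| Heavy tails (t, 3 df) | 0 | 72.7 | 91.0 | 89.4 | 76.4 |
| Heavy tails (t, 3 df) | 0.3 | 77.5 | 87.7 | 87.1 | 68.5 |
| Heavy tails (t, 3 df) | 0.5 | 83.8 | 82.7 | 85.9 | 54.0 |
| Heavy tails (t, 3 df) | 0.7 | 93.1 | 73.2 | 88.0 | 32.4 |

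A separate simulation of scores bounded at zero (44 per group, 0.9 cm, r = 0.3 to 0.5) gave ANCOVA about 69% to 76% against 66% for rank-sum. The switch fired in every trial.

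**Can the effect itself trip the rule?** Normal scores with SD 1.7 were clipped to 0–10 cm, with 44 per group and a true difference of 3 cm. With assumed control means of 4, 5 and 6 cm, the pooled variable is flagged non-normal in nearly 100%, about 57% and about 10% of trials. The within-arm residuals are flagged in about 52%, 19% and 5%. With no effect the pooled variable is flagged in about 4%.

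**Type I error.** ANCOVA alone gave 4.3% to 5.5% in every scenario, so the fallback is not needed for validity. The fixed switch gave 4.2% to 5.5%. Keeping the better of the two p-values would give about 5.5% to 8.1%.

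**The case against.** A reader might infer that the fallback generally costs power. The documents do not support that. The normal-data comparison describes a setting where a normality switch seldom fires: at r = 0.5 the switch rule as a whole loses under one point (80.1% to 79.4%). Where it does fire, the rank-sum test is clearly ahead at low correlation, for example 82.4% to 67.8% under skew at r = 0. Low correlation is plausible, because entry requires a baseline VAS of at least 4 cm, which narrows the baseline range. At the stated 3 cm difference there is no loss. All of this stands and limits the power argument.

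A reader might also infer that a data-driven choice inflates false positives. A fixed switch does not. Inflation would need someone to keep the better p-value, and the article says that the statistician is blinded to group.

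The rank-sum test could be applied to change from baseline, and the article does not say whether SD 1.7 refers to scores or to change. If it refers to scores, change has SD 1.7 × √(2(1 − r)). That is 1.7 at r = 0.5, no gain over raw scores, and 1.317 at r = 0.7, still above ANCOVA's 1.214. If 1.7 is the SD of change, ANCOVA's residual SD is 1.7 × √((1 + r)/2) = 1.567 at r = 0.7. Its power is then about 76%, against 67% for rank-sum on change. The advantage shrinks but remains.

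Finally, covariates and normality checks are commonly left to an analysis plan, which is not shown. Their absence is not the point. The article states a switching rule outright and leaves the primary VAS inside it.

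**Conclusion.** The point holds as a defect in how the primary analysis is fixed, and it merits a change. Three parts need no assumed correlation: the data choose the primary test, the trigger examines the variable rather than the residuals, and the fallback yields no adjusted difference in cm.

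The power cost is conditional. When the fallback is used on normal data at 0.9 cm, it is about 6, 14 and 26 points at r = 0.3, 0.5 and 0.7. Under gamma skew it is about 4 points at r = 0.5 and 17 at r = 0.7, and it becomes a gain at r of about 0.3 or less. With heavy tails the tests are about equal at r = 0.5. There is no cost at 3 cm. These figures rest on δ0 = 3.9, SD 1.7 for outcome scores, a two-sided 5% test, baseline VAS as the covariate, and assumed values of r. The planned rule is not invalid: no type I error inflation follows from a switch applied mechanically.

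**What to change.** State that the primary VAS analysis is ANCOVA adjusted for baseline VAS whatever the observed distribution, and report the adjusted mean difference in cm with robust or bootstrap confidence limits. Exempt the primary VAS from the rank-sum rule. Use a rank-based test, preferably one that keeps baseline such as rank ANCOVA, only as a sensitivity analysis.

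This costs wording, with no extra patients or visits. The article says the trial is still recruiting, so the change can be made before unblinding. The downside is some loss of efficiency against a rank test if scores prove very skewed or heavy-tailed and the baseline correlation is low. The sensitivity analysis would show this.

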#### Pain diary

Pain diaries will be used to record the specific time and frequency of pain attacks, the duration of pain, the changes of intensity, the start time of pain relief and any medication used for patients. Pain diaries will be assessed at the baseline period, the first, second and third menstrual cycles and at follow-up.

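### Analgesic users are excluded from the analysis without restriction, which contradicts the stated intention-to-treat analysis and can bias the pain comparison in a direction the protocol does not settle

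*Protocol article*

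**What the plan says.** All the rules at issue stand in one paragraph of the protocol article, under Sample size calculations and statistical analysis.

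- Population: "The data will be subjected to intent-to-treat analysis".
- Primary comparison: "The between-group difference will be compared by analysis of covariance", with a rank-sum test for variables that are not normally distributed.
- Missing values: last observation carried forward.
- Analgesic users: "If participants have taken analgesics during the trial, they will be excluded from the analysis". The sentence continues: "the rate difference of outcomes between the two groups will be analyzed".

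The exclusion has no limit by drug, amount or timing. By the Abstract, the trial spans three cycles of treatment and three of follow-up.

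Under Primary outcome: "The primary outcome is pelvic pain that include dysmenorrhea, intermenstrual pain and dyspareunia", scored on a VAS. Under Pain diary, the diaries record "any medication used for patients" at baseline, in each treatment cycle and at follow-up.

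**The concern.** Intention-to-treat means that every randomised patient is analysed in the assigned group. A rule that removes patients for something they do after randomisation cannot also govern that analysis.

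The event chosen makes matters worse. Women enter with a VAS of at least 4 cm, so analgesic use is foreseeable, and it is likely to depend on the pain that the trial measures. Removing users therefore selects patients partly on the primary outcome. Randomisation no longer protects the comparison among those who remain.

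At stake are the size of the estimated effect, possibly its direction, and the number of patients left in a trial of 106. Two incompatible rules also leave the analysis population open to choice once the data are known.

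**Working it through.** **1. The text.** The intention-to-treat sentence and the exclusion both refer to the analysis without qualification. Carrying the last observation forward fills gaps for patients who stay in the data set; it does not restore patients removed by rule. The rate difference names no binary outcome and does not return anyone to the VAS comparison. Nothing elsewhere in the article reconciles the two sentences. The contradiction needs no calculation.

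**2. The plan's own sample size.** Inputs from the same section: SD 1.7, difference 3, power 80%, significance level 0.05, at least 44 per group, 53 after a 20% allowance described only as dropout. With a margin of 0, the printed formula gives:

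- two-sided: 2 × [(1.960 + 0.842)/3]² × 1.7² = 5.04, so 6 per group
- one-sided: 2 × [(1.645 + 0.842)/3]² × 1.7² = 3.97, so 4 per group

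Neither is 44. Solving the two-sided form for 44 gives a net difference of 1.7 × √(2/44) × 2.802 ≈ 1.02 cm. That mismatch is a separate matter. It is used here only to justify looking at true differences of both about 1 cm and 3 cm.

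**3. Illustration of the selection.** Assumed, because the article gives no analgesic-use rate and no control mean: VAS is normal with SD 1.7, mean 5 cm in controls and 5 minus the true difference under acupuncture. The probability of use is 1/(1 + exp[−s(VAS − c)]), with midpoint c of 4 or 5 cm and slope s of 0.5 or 1 per cm, the same in both arms. Analgesics themselves do not change VAS. Users are removed and the means compared (simulation, millions of patients per arm). Patients left = 44 × (1 − proportion excluded).

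| True difference (cm) | c | s | Controls excluded | Acupuncture excluded | Left of 44 (control / acupuncture) | Difference seen (cm) |
|---|---|---|---|---|---|---|
| 1.0 | 4 | 0.5 | 61% | 50% | 17 / 22 | 0.87 |
| 1.0 | 4 | 1 | 66% | 50% | 15 / 22 | 0.67 |
| 1.0 | 5 | 0.5 | 50% | 39% | 22 / 27 | 0.87 |
| 1.0 | 5 | 1 | 50% | 34% | 22 / 29 | 0.70 |
| 3.0 | 4 | 0.5 | 61% | 30% | 17 / 31 | 2.61 |
| 3.0 | 4 | 1 | 66% | 20% | 15 / 35 | 2.13 |
| 3.0 | 5 | 0.5 | 50% | 21% | 22 / 35 | 2.65 |
| 3.0 | 5 | 1 | 50% | 11% | 22 / 39 | 2.28 |

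With a true difference of 0, the difference seen is 0 in all four settings.

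**4. Power after exclusion** (two-sided 5%, SDs as found among non-users). Worst case at 1.0 cm: SE = √(1.38²/14.9 + 1.40²/22.0) = 0.466, and 0.669/0.466 − 1.96 = −0.52, so power is about 30% by the normal approximation and 29% with the t distribution. Across the four settings it is about 29–46%. With all 44 per group kept and a true 1.0 cm difference it would be about 79%. At 3 cm the worst case is SE = √(1.38²/14.9 + 1.51²/35.0) = 0.439, and 2.131/0.439 − 1.96 = 2.89, so power is above 99%.

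**5. Use that differs by arm** (slope 1, difference taken as control minus acupuncture).

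- True 1.0 cm: midpoints of 4 in controls and 5 under acupuncture give 0.37 cm; the reverse gives 1.00 cm, which is no bias.
- True 0: the same two settings give about −0.33 and +0.33 cm.

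**The case against.** The best defence is that the exclusion comes after the intention-to-treat and covariance sentences and is joined to a separate analysis of rates. It could be a clumsy description of an additional analysis in non-users. The words do not say so, and an unseen analysis plan cannot excuse a rule that the article states. This reading makes the fault an unreconciled conflict; it does not remove it.

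Four stronger readings are tempting, and the document supports none of them.

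- A reader might infer that the exclusion always dilutes the effect. That holds in the model only when use tracks pain alike in both arms; with arm-specific use, dilution ranged from strong to none, and a null could be shifted either way. Equally, the document gives no ground for saying that the rule favours acupuncture.
- A reader might infer that the trial loses its power. At the stated 3 cm difference it does not. The loss is material near 1 cm.
- A reader might take the rate difference as a replacement for the covariance analysis that does not suit a continuous VAS. The text does not call it a replacement, and the section cites a minimal important improvement from which a responder rate could be formed. The fault is that the outcome is undefined.
- A reader might take the exclusion percentages as forecasts. They come entirely from the assumed curve.

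It is also fair to say that an analysis that ignores analgesic use has its own weakness: scores lowered by an analgesic are counted as they stand.

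**Conclusion.** The concern holds in this form. The article states two rules for the analysis population that cannot both apply to the primary comparison, and one of them selects on a post-randomisation event that plausibly depends on the outcome. That conclusion rests on the text alone and should be put right before analysis.

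The size and direction of the bias are not fixed by the document. Under the symmetric assumptions above, a true 1.0 cm difference shrinks by 13–33%, with 15–22 controls and 22–29 acupuncture patients left of 44. A true 3 cm difference shrinks to about 2.1–2.65 cm, with 15–22 controls and 31–39 acupuncture patients left. A true null is unbiased under those assumptions, but not if use differs by arm for reasons other than pain.

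**What to change.** 1. Delete the exclusion from the primary analysis. Analyse the VAS of every randomised patient in the assigned group, whatever analgesic was taken, and say so explicitly.
2. Report analgesic use by arm from the pain diary as a secondary outcome. Give the rate difference there, with its numerator and denominator defined.
3. Add one prespecified sensitivity analysis that treats analgesic use as an unfavourable outcome, for example as non-response or as the worst recorded score.
4. Label any analysis limited to non-users as supplementary.

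The cost is a change of wording, since the diary already collects the medication data. The downside is real: if controls take more analgesics and these lower VAS, the primary estimate is diluted by an amount that the document does not allow to be computed. The sensitivity analysis would show how far the conclusion depends on this. The change concerns the analysis only and proposes no rule on taking analgesics.

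### The sample size uses a one-sided 5% critical value, while the final rule is an unqualified P < 0.05, two-sided by convention, so the 80% power belongs to a more lenient test than the one ordinarily reported

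*Protocol article*

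**What the plan says.** Everything relevant stands in one section of the protocol article, Sample size calculations and statistical analysis.

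- **Aim.** It is worded with a direction: "This trial will use a clinical-superiority design that aims to verify that the curative effect of acupuncture is better than that of comfort needles".
- **Error rates for sizing.** "the statistical power is 80% and the significance level is 0.05". No sidedness is given.
- **Critical value.** The formula has Z with subscript 1-α, not 1-α/2, and the legend repeats it: "Z*_1-α_ is Type I error, *Z*_1-β_ is Type II error".
- **Effect and spread.** The section proceeds by "assuming the standard deviation (SD) to be 1.7 and the difference between two treatment effect to be 3".
- **Margin.** The formula subtracts a δ0 that is never given a value. Just before it the section reports: "The minimal important difference (MID) for improvement on the VAS was found to be − 3.9 cm and/or − 49" (the last figure is a percentage).
- **Result.** 44 per group, raised to 53 per group (106 in total) for 20% dropout.
- **Analysis.** "The between-group difference will be compared by analysis of covariance", with a rank-sum test for variables that are not normally distributed.
- **Decision rule.** "Statistical significance will be set at *P* < 0.05". Again no sidedness is given.

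**The concern.** The value 0.05 appears twice and, as ordinarily read, means two different error rates. In the sizing formula it yields a critical value of 1.645, which is a one-sided 5% test and equals a two-sided 10% test. In the analysis paragraph it is attached to an analysis of covariance, whose F test has no direction, or to a rank-sum test, whose P value is normally reported two-sided. The matching critical value there is 1.960.

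Two things depend on this. First, the stated 80% power at 44 per group was obtained for the more lenient rule and does not carry over to the stricter one. Second, a result in favour of acupuncture with a two-sided P between 0.05 and 0.10 is positive under the sizing rule and not significant under the ordinary reading of the analysis rule. If the sidedness were settled only after the data were seen, the chance of a false claim in favour of acupuncture could be 5% instead of the 2.5% that a two-sided 0.05 test allows.

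**Working it through.** **Inputs.** All are from the section named above: SD 1.7, expected difference 3, α = 0.05, power 80%, 44 per group before dropout, 53 per group recruited. δ0 is not printed; 3.9 is inferred as the value that reproduces 44. The Z for 80% power is 0.8416.

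**Step 1. Reproduce the plan's figure.** The article's formula is N = 2 × [(Z_α + 0.8416)/d]² × 1.7², with d = |δ - δ0|. Here 2 × 1.7² = 5.78.

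| d (cm) | One-sided 5% (1.645) | Two-sided 5% (1.960) |
|---|---|---|
| 0.9, from 3 and 3.9 | 5.78 × (2.4865/0.9)² = 44.1 | 5.78 × (2.8016/0.9)² = 56.0 |
| 3, with δ0 = 0 | 5.78 × (2.4865/3)² = 4.0 | 5.78 × (2.8016/3)² = 5.0 |

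Only the one-sided value at 0.9 cm matches 44 (strict rounding up would give 45). The arithmetic thus agrees with the printed subscript and does not suggest a misprint for 1-α/2.

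**Step 2. Test how firm that match is.** A two-sided 5% test also gives 44 at d = 1.015 cm, and 45.4 at d = 1.0 cm, but no pair of printed figures yields either difference. The legend describes S² as the SD. Putting 1.7 in unsquared at d = 0.9 and 80% power gives 26.0 one-sided and 32.9 two-sided. That route reaches 44.1 two-sided only at 90% power, which contradicts the stated 80%. The match is therefore supporting evidence, and the main evidence is the subscript.

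**Step 3. Power at 0.9 cm.** The standard error is 1.7 × √(2/n): 0.362 cm at 44 and 0.330 cm at 53 per group. Normal-approximation power is Φ(0.9/SE - Z_α).

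| n per group | One-sided 5% | Two-sided 5% |
|---|---|---|
| 44 | Φ(2.483 - 1.645) = 79.9% (t test 79.4%) | Φ(2.483 - 1.960) = 70.0% (t test 69.0%) |
| 53, no dropout | Φ(2.725 - 1.645) = 86.0% (t test 85.6%) | Φ(2.725 - 1.960) = 77.8% (t test 77.0%) |

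On this difference the two-sided test stays below 80% even if all 106 patients are analysed.

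**Step 4. Power at the stated 3 cm against zero.** At 44 per group, 3/0.362 is about 8.3 standard errors, far beyond either 1.645 or 1.960. Power exceeds 99.9% with either sidedness.

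**Step 5. Where the two rules part.** With 53 per group, the smallest observed difference that reaches significance in a t test is 0.548 cm one-sided and 0.655 cm two-sided. A result between these two values passes one rule and fails the other.

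**Assumptions for steps 3 to 5.** A two-sample comparison against zero, SD 1.7, and no gain credited to baseline adjustment.

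**The case against.** The strongest reply is that nothing here is contradictory in words. The article never says two-sided. A directional aim, a one-sided critical value, a 0.05 level and P < 0.05 fit together if a one-sided 5% test is meant, and the sidedness of the final test may be given in a full protocol or analysis plan that is not shown. This stands in part. A reader might infer an explicit contradiction, and the text does not support that: the two-sided reading is convention. But the point is not silence. The article commits to a one-sided critical value and to a power figure derived from it, and nowhere declares a one-sided test. A directional aim is not such a declaration, since most superiority trials with a directional aim are tested two-sided.

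The second reply concerns size. The 0.9 cm rests on an inferred δ0 and is a distance from a margin, whereas the power figures in step 3 treat it as a difference from zero. The difference the plan states is 3 cm. A reader might infer from 70% and 77% that the trial is underpowered, and the document does not support that either: at 3 cm against zero, power exceeds 99.9% under both rules, and an observed difference between 0.55 and 0.65 cm would be very improbable, about 7 standard errors below 3. This reply stands in full as a limit on the consequence. It does not remove the mismatch, because 1.645 against 1.960 does not depend on the difference entered. Nor does it rescue the stated 80%, because 44 was not derived from 3 cm against zero.

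The missing value of δ0, and an expected effect smaller than the quoted minimal important difference, are a separate matter. Settling them would leave the sidedness open.

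**Conclusion.** The point holds in a limited form. The sizing is one-sided at 5%, shown by the printed subscript and supported by the arithmetic (44.1 against 56.0). The decision rule is an unqualified P < 0.05 that would ordinarily be run and reported two-sided. The stated 80% power at 44 per group is therefore not the power of the test as ordinarily run, and a result in favour of acupuncture with two-sided P between 0.05 and 0.10 has no settled interpretation.

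The size is conditional. On the inferred 0.9 cm, two-sided power is 69–70% at 44 per group and 77–78% at 53, instead of 79–80% and 86% one-sided. On the stated 3 cm against zero, sidedness makes no practical difference to power. Confidence is medium, because the two-sided reading is convention and δ0 is inferred. The correction is still worth making: it affects both a stated figure and the decision rule, and costs very little.

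**What to change.** Use one sidedness in both places, and settle it before unblinding.

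- State that the primary comparison is tested at two-sided 0.05 and reported with a 95% confidence interval.
- Replace Z at 1-α by Z at 1-α/2 in the formula and its legend.
- Restate the power of the fixed 106 patients for that test, naming the difference and the null value it refers to. Without these two, the figure could be read as anything from about 70% (0.9 cm, 44 per group) to above 99.9% (3 cm against zero).

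If a one-sided 5% test is really intended, declaring it in the analysis paragraph would also remove the mismatch, at the price of an openly stated 5% false-positive rate in favour of acupuncture.

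The cost is a short amendment and a restated power figure, with no extra patients. The downside is that, if 0.9 cm is kept as the target, the stated power becomes less favourable.
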